# Efficacy of Hwangryunhaedok-tang (Huang-lian-jie-du-tang, Oren-gedoku-to) for patients with hyperlipidemia: a study protocol for a randomized, double-blind, placebo-controlled, parallel, investigator-initiated clinical trial

**DOI:** 10.1186/s13063-020-04695-3

**Published:** 2020-08-27

**Keywords:** Herbal medicine, Hwangryunhaedok-tang (Huang-lian-jie-du-tang, Oren-gedoku-to), Hyperlipidemia, Korean traditional medicine, Randomized controlled trial

## Abstract

**Background:**

The prevalence of hyperlipidemia continues to increase due to aging and lifestyle changes. Statins are currently used as the first choice for treating hyperlipidemia, but are limited by adverse reactions. Hwangryunhaedok-tang (HHT) has received attention as a promising intervention for hyperlipidemia through a few experimental and clinical trials. This study aims to explore the feasibility, effectiveness, and safety of HHT for hyperlipidemia treatment.

**Methods:**

This is a study protocol for a randomized, double-blind, placebo-controlled, parallel, investigator-initiated, pilot clinical trial held in Daejeon, Republic of Korea. Thirty patients with hyperlipidemia will be randomly allocated to HHT or placebo granule groups in equal proportions. Participants will be administered HHT or placebo granules three times per day for 8 weeks and followed up for another 4 weeks. The primary outcome is low-density lipoprotein cholesterol at 8 weeks from the commencement of treatment. Other blood lipid parameters, biomarkers of atherosclerosis, the degree of arteriosclerosis, blood glucose parameters, blood pressure, anthropometric parameters, health-related quality of life, and the changes in the general symptoms of cold and hot patterns will be measured as secondary outcomes. Adverse events and laboratory test results will be investigated to assess the safety. Changes in the gut microbiome before and after intervention will also be assessed as an exploratory outcome through next-generation sequencing. Data will be recorded in electronic case report forms and analyzed using SAS® Version 9.4.

**Discussion:**

This is a rigorously designed pilot clinical trial to explore the effect and safety of Hwangryunhaedok-tang compared to placebo control for patients with hyperlipidemia, thereby potentially facilitating better management of hyperlipidemia. The results of this pilot study could form the foundation for a future large-scale, confirmatory clinical trial.

**Trial registration:**

Clinical Research Information Service KCT0004564. Registered on December 18, 2019

## Background

Hyperlipidemia refers to high blood levels of total cholesterol (TC), low-density lipoprotein cholesterol (LDL-C), or triglyceride (TG) [1]. Recently, the prevalence of hyperlipidemia has increased due to aging, diet, and lifestyle changes. In the USA, it is reported that 38.2% of adults have elevated TC levels [2]. In particular, hypercholesterolemia showed a significant increase, and the prevalence of hypercholesterolemia in the Republic of Korea more than doubled over 10 years from 10.7% in 2007 to 21.5% in 2017 according to the National Health and Nutrition Survey data in the Republic of Korea [3, 4]. In addition, attention has been focused on the correlation between hyperlipidemia and coronary artery disease. One of the reasons for the increase in coronary artery disease in the Republic of Korea despite the rapid decrease in cerebrovascular diseases is estimated to be an increase in hyperlipidemia [4]. It is also estimated that hypercholesterolemia is responsible for 56% of ischemic heart diseases and 18% of strokes worldwide [5].

Since hyperlipidemia usually has no symptoms, a screening test is essential and primary treatments include lifestyle changes such as diet control, exercise, and smoking cessation [4]. The use of conventional medication is based on a comprehensive assessment of cardiovascular disease risk and LDL-C levels [4]. In particular, conventional medication should be considered when LDL-C levels are still high after several weeks or months of lifestyle changes in patients without cardiovascular diseases [4]. Currently, statins are used as the first choice medications for treating hyperlipidemia; however, adverse reactions such as dyspepsia, heartburn, abdominal pain, liver toxicity, myalgia, rhabdomyolysis, and diabetes have emerged as problems [6, 7]. Therefore, the demand for treatment using botanic materials that can control blood lipid levels from the early stage of hyperlipidemia and can be safely taken for a long time is increasing.

Hyperlipidemia is regarded as a category of phlegm-dampness and static blood in East Asian traditional medicine (EATM) theory and treatment methods such as “dispel phlegm and eliminate dampness,” “activate blood and resolve stasis,” “tonify and replenish the middle qi,” and “clear heat and purge fire” have been proposed [8, 9]. Hwangryunhaedok-tang (HHT; Huang-lian-jie-du-tang in Chinese, Oren-gedoku-to in Japanese) is an herbal prescription comprised of four herbs that clear heat, dry dampness, purge fire, and detoxify and therefore, according to the EATM theory, HHT can treat hyperlipidemia. Additionally, it is widely used for cardiovascular and cerebrovascular diseases, such as hypertension, hyperlipidemia, and stroke in EATM [10, 11]. It has been reported that HHT showed LDL-C and TC lowering effects by inhibiting 3-hydroxy-3-methyl-glutaryl-coenzyme A (HMG-CoA) reductase in animal models of hyperlipidemia [12]. In addition, in the high-cholesterol animal model, the administration of HHT for 8 weeks significantly prevented the progression of thoracic aortic plaque with an anti-oxidative effect [13]. In particular, *Berberine*, a component of HHT, has been reported to reduce TC and LDL-C levels and increase high-density lipoprotein cholesterol (HDL-C) levels in animals and humans through mechanisms such as absorption of cholesterol in the intestine, removal of LDL receptor-mediated LDL-C, and conversion of cholesterol into bile [14]. In a randomized controlled trial (RCT) comparing HHT and statins in patients with hyperlipidemia, both groups exhibited significantly decreased TC, TG, and LDL-C and significantly increased HDL-C after treatment, compared to the levels before treatment. However, there was no significant difference between the two groups showing results in favor of HHT after treatment, with the exception of the fasting blood glucose level [15]. Furthermore, when HHT plus statin and statin alone were compared in patients with both hypertension and hyperlipidemia, inflammatory factors were significantly improved in the HHT plus statin group [16].

Although there is experimental and clinical evidence of the application of HHT for the treatment of hyperlipidemia as described above, and HHT has been used frequently in clinical settings of EATM, no studies have been conducted to evaluate its effect on blood lipid metabolism compared to placebo in patients with hyperlipidemia. Therefore, the aim of this pilot study is to explore the feasibility and preliminary effectiveness and safety of HHT for patients with hyperlipidemia.

## Methods/design

### Study design

This is a study protocol for a randomized, double-blind, placebo-controlled, parallel, investigator-initiated, pilot clinical trial. The study period will include 8 weeks of medication and 4 weeks of follow-up. The study procedure is summarized in the Consolidated Standards of Reporting Trials (CONSORT) diagram (Fig. 1), and the schedule of enrolment, intervention, and assessments is summarized in Table 1. The trial will be performed according to the Declaration of Helsinki and Good Clinical Practice Guidelines. In addition, the study protocol follows the CONSORT Extension for Chinese Herbal Medicine Formulas 2017 [17] and Standard Protocol Items: Recommendations for Interventional Trials 2013 statement (Additional file 1) [18].

**Fig. 1 Fig1:**
[figure not shown]
Flow diagram of the trial

**Table 1 Tab1:**
[figure not shown]
Schedule of enrolment, interventions, and assessments

*Abbreviations*: *ABI* ankle-brachial index, *baPWV* brachial-ankle pulse wave velocity, *BIA* bioelectrical impedance, *EQ-5D-5L* five-level EuroQol-5 dimensions, *HHT* Hwangryunhaedok-tang, *IPAQ* international physical activity questionnaire

*Including blood lipid parameters, biomarkers of atherosclerosis, blood glucose parameters, hematological test, thyroid hormone test, and liver and renal function test, depends on the time point

^+^Including human chorionic gonadotropin urine test only for women in their childbearing years at the screening visit

### Recruitment

The study will be performed at the Daejeon Korean Medicine Hospital of Daejeon University. The trial will be advertised through offline and online recruitment notices, including posters and webpages. Investigators will provide research information such as objectives, procedures, and potential benefits and risks to participants through standardized interviews prior to their participation and informed consent will be obtained from all participants. Participants will be allowed to withdraw from the study at any time without disadvantage and will be immediately notified when new information regarding the study is obtained.

### Inclusion criteria

Adults aged 19 years or over but under 65 years at the screening visit130 mg/dl ≤ baseline LDL-C levels ≤ 250 mg/dlThose who have voluntarily signed written informed consent forms approved by the institutional review board (IRB) after sufficient explanation about this study

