### Randomization and allocation concealment

An independent statistician ([name]) will generate a random assignment code using the block randomization method in block sizes of 2 and 4 with no stratification in SAS® Version 9.4 (SAS Institute Inc., Cary, NC). Participants that satisfy the eligible criteria will be assigned to the HHT or placebo granule group at the baseline visit (Week 0), with a 1:1 allocation ratio. The generated code will be sealed in opaque envelopes and stored in double-locked cabinets. We will maintain allocation concealment throughout the study period by giving participants identically packaged, consecutively numbered drug containers.

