### Data collection

#### Background information

Investigators will collect the demographic and clinical information of participants and perform vital sign measurement and laboratory tests only for those participants who voluntarily sign the informed consent form at the screening visit. Demographic data include age, gender, height, weight, smoking history, and alcohol consumption. General clinical information includes medical history, treatment history, concomitant disease, and medication. The personal information of the participants will be de-identified by using a coded ID number and will be stored securely at the institution to protect confidentiality and ensure access is limited to the investigators involved in the study.

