### Efficacy outcomes

The primary outcome is the blood level of LDL-C, which will be measured at baseline and 4, 8, and 12 weeks after randomization. In this study, the primary endpoint is 8 weeks post-treatment. The secondary outcomes are other blood lipid parameters including TC, TG, HDL-C, non-HDL-C, non-HDL-C/HDL-C, apolipoprotein (Apo) A1, Apo B, Apo B/Apo A1, lipoprotein (a), and atherogenic index of plasma (Log(TG/HDL-C), and atherosclerosis biomarkers including high-sensitivity C-reactive protein (hs-CRP), fibrinogen, and homocysteine, which will be measured at baseline and 4, 8, and 12 weeks after randomization. Using VP-1000plus (OMRON Healthcare Co., Kyoto, Japan), the degree of vessel hardening will be assessed through brachial-ankle pulse wave velocity (baPWV). The degree of narrowing due to vascular lesions will be assessed by measuring the blood pressure difference between the ankle and arm using the ankle-brachial index (ABI) to determine the degree of arteriosclerosis. Blood glucose parameters including fasting glucose and HbA1c, blood pressure, and anthropometric parameters including body weight, body fat percentage, body fat mass, skeletal muscle mass, waist circumference, hip circumference, and waist-to-hip ratio will also be measured. The health-related quality of life before and after taking the investigational product will be measured using the five-level EuroQol-5 dimensions (EQ-5D-5L). The EQ-5D-5L is composed of 25 items in five domains including mobility, self-care, usual activities, pain/discomfort, and anxiety/depression. Participants will respond to each item with five response levels: no problems (level 1), slight, moderate, severe, and extreme problems (level 5) [23]. The Korean version of EQ-5D–5 L will be used after permission from the EuroQol Research Foundation. Blood lipid parameters, atherosclerosis biomarkers, the degree of arteriosclerosis, blood glucose parameters, blood pressure, anthropometric parameters, and EQ-5D-5L will be measured at baseline and 4, 8, and 12 weeks after randomization.

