### Statistical analysis

An independent statistician will conduct statistical analysis using SAS® Version 9.4 (SAS Institute Inc., Cary, NC). In principle, efficacy analysis will be conducted using a full analysis set according to the intention-to-treatment principle, including all randomly assigned participants receiving at least one evaluation after the investigational product has been prescribed at least once. If necessary, per protocol set (PPS) analysis will also be conducted including only participants who have completed the entire process as described in the protocol and have no significant violations. Participants less than 70% compliant with the investigational product will be excluded from the PPS analysis. Safety analysis will include all data obtained from participants who have taken at least one investigational product.

The demographic and general clinical characteristics of participants will be summarized by group. Continuous data will be presented as mean and 95% confidence intervals or median according to the distribution of the data and dichotomous data as frequency and percentage. Continuous data will be analyzed using the independent *t* test or Wilcoxon rank sum test, and dichotomous data will be analyzed using the chi-square test or Fisher’s exact test.

The primary outcome in this study is the mean change in LDL-C from baseline to week 8. A two-sided test with a significance level of 5% will be performed using an analysis of covariance with baseline as the covariate and the treatment group as the fixed factors. The intra-group changes of outcome measures from baseline to post-treatment will be analyzed using paired *t* test or Wilcoxon signed rank test for continuous variables and the chi-square test or Fisher’s exact test for dichotomous variables. Furthermore, repeated measures analysis of variance will be used to compare the differences in trends between visits in each group. Missing values will be replaced with the multiple imputation method. If necessary, a subgroup analysis can be performed by categorizing the participant’s initial characteristics at the screening or baseline visit.

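### The LDL-C value that admits a participant is, on the literal text, also the analysis baseline: the between-arm test stays valid, but within-arm changes carry regression to the mean and some precision is lost

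*Protocol article*

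**What the plan says.** - **Entry.** Protocol article, Inclusion criteria: age is judged at the screening visit, but the 130 to 250 mg/dl window is set on "baseline LDL-C levels".
- **Timing of baseline.** Randomization and allocation concealment: those who meet the criteria "will be assigned to the HHT or placebo granule group at the baseline visit (Week 0), with a 1:1 allocation ratio".
- **LDL-C schedule.** Efficacy outcomes: "The primary outcome is the blood level of LDL-C, which will be measured at baseline and 4, 8, and 12 weeks after randomization". No screening LDL-C is listed.
- **Primary analysis.** Statistical analysis: the outcome is the mean LDL-C change from baseline to Week 8, tested at two-sided 5% "using an analysis of covariance with baseline as the covariate and the treatment group as the fixed factors". The same section plans paired tests of change from baseline within each group.
- **Screening.** Background information: investigators "perform vital sign measurement and laboratory tests only for those participants who voluntarily sign the informed consent form at the screening visit". Statistical analysis treats the two visits as distinct ("at the screening or baseline visit"). The Table 1 footnote includes blood lipids in a list of laboratory tests whose content, down to "liver and renal function test, depends on the time point", varies by visit.

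**The concern.** A measured LDL-C is the person's underlying level plus within-person variation. Requiring a reading of at least 130 mg/dl preferentially admits people whose reading was high by chance, so their next reading is lower on average even without treatment. If the entry reading is also the baseline, that fall becomes part of every change from baseline.

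Two things are at stake. First, the planned intra-group paired tests can show an apparent improvement in an arm where nothing happened. Second, adjusting for one reading that was itself used for selection leaves more residual variance than two pre-treatment readings would, in a trial with 15 participants per arm.

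**Working it through.** **1. The plan's own figure.** Twelve per group with 20% dropout: 12 / (1 − 0.20) = 15 per group, 30 in total. This reproduces. The article states no power, effect size or LDL-C variance.

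**2. Reading the sections together.** Entry is on the baseline value, baseline is Week 0, change and covariate use baseline, and no screening LDL-C is scheduled in the text. One shared value is the literal reading. Against it, laboratory tests are done at screening, and participants must already qualify when they reach Week 0. The text does not settle the matter.

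**3. Model and assumptions (none from the documents).** True level T has mean 120 to 140 and SD 33 mg/dl in those screened. Each reading adds independent error with SD w = 10 to 15. True drift to Week 8 has SD d = 0 to 10. X1 is the entry reading (130 to 250), X2 a separate Week 0 reading, Y the Week 8 reading without treatment.

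**4. Fall caused by selection.** Expected fall = (1 − λ) × (mean of admitted X1 − population mean), with λ = 33² / (33² + w²).
- Population mean 130, w = 10: 1 − λ = 100 / 1189 = 0.084. Admitted readings average about 27.5 above 130. Fall = 0.084 × 27.5 ≈ 2.3 mg/dl.
- Population mean 130, w = 15: 1 − λ = 225 / 1314 = 0.171. Admitted readings average about 28.8 above 130. Fall ≈ 4.9 mg/dl.
- Simulation over the full range: 1.8 to 6.1 mg/dl in both arms. Change measured from X2 is about 0. Of those admitted, 10% to 23% have X2 below 130.
- A wider set of assumptions (mean 115 to 150, SD 25 to 32, w = 8 to 15) gives 0.9 to 8.9 mg/dl.

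**5. Paired test in an untreated arm.** Simulated at 15 per arm, for settings within the wider set, with no true change: rejection in about 6% to 19% of trials, against a nominal 5%.

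**6. Between-arm ANCOVA with one shared value.** In the same simulations, type I error is 0.047 to 0.049, and a true effect of −15 mg/dl is recovered as −14.97 to −15.04.

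**7. Precision.** Residual variance with X1 alone = 1 / (1/33² + 1/w²) + d² + w². With both readings, the first term becomes 1 / (1/33² + 2/w²).
- w = 10, d = 0: (47.8 + 100) / (91.6 + 100) = 147.8 / 191.6 = 0.77.
- w = 10, d = 10: 247.8 / 291.6 = 0.85.

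| Primary model | Residual variance relative to one shared value |
|---|---|
| Separate Week 0 value as the only covariate | 0.91 to 0.97 |
| Week 8 LDL-C on the mean of screening and Week 0 | 0.77 to 0.85 |
| Change from Week 0 on both values as two covariates | 0.77 to 0.85 |
| Change from Week 0 on the two-value mean only | 1.01 to 1.04 |

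A ratio of 0.77 to 0.85 corresponds to 1/0.85 to 1/0.77, that is 18% to 30% more participants. Against a separate Week 0 covariate alone, the reduction is about 10% to 20%.

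**8. Why the last row fails.** Fitting Y − X2 = a + b(X1 + X2)/2 is the same as Y = a + (b/2)X1 + (1 + b/2)X2. The weight on X2 is forced to exceed that on X1 by exactly 1, whereas the best weights are equal (about 0.48 each at w = 10).

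**The case against.** The strongest reply is that double use is not established. Baseline LDL-C in the criterion may simply mean the untreated level checked at screening, with a fresh Week 0 draw as the analysis baseline. Several exclusion criteria need laboratory results before randomisation, and Table 1 may show lipids at both visits. This stands as far as proof goes. It does not rescue the wording: if screening decides entry, the criterion names the wrong visit; if Week 0 decides, the result must be back before randomisation at that visit.

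A reader might infer that the primary comparison is biased or its 5% level inflated. The documents do not support that. Selection precedes randomisation and acts alike on both arms, so the fall cancels in the between-arm difference, as step 6 shows.

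A reader might also infer that the spurious fall will distort the size of the next trial. The Discussion says only that the sample size will be calculated from this study's results. A placebo-controlled trial would normally be sized on the between-arm difference and its SD.

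Finally, one baseline covariate is ordinary practice, and separating entry from baseline saves only about 3% to 9% of residual variance. That is fair. Most of the gain comes from using two readings, which is an efficiency option and not the repair of an error.

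**Conclusion.** The point holds in limited form. The text, read literally, uses one LDL-C value for entry, change and covariate; this is likely but unproven without the body of Table 1. If so, within-arm changes contain a fall of roughly 2 to 6 mg/dl, and untreated-arm paired tests reject about 6% to 19% of the time. The primary between-arm ANCOVA is valid and loses only precision. All sizes depend on the assumed population mean, between-person SD, within-person SD and drift. Minor priority: the trial is a 30-person pilot with no power target, and its Discussion already says that 15 per group may be too few for a definite conclusion.

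**What to change.** 1. **Inclusion criteria:** state that the 130 to 250 mg/dl window, with its limits unchanged, applies to LDL-C at the screening visit.
2. **Statistical analysis, change:** define change from a separate pre-dose Week 0 LDL-C that plays no part in eligibility. Say that intra-group changes are descriptive and are not read as treatment effects.
3. **Statistical analysis, primary model:** either fit change with Week 0 and screening LDL-C as two covariates, or fit the Week 8 LDL-C with their mean as covariate. Do not combine change from Week 0 with the two-value mean as the only covariate.

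**Cost.** Mainly wording. If lipids are not already drawn at both visits, one extra LDL-C assay per participant. Entering both covariates uses one residual degree of freedom (30 − 3 = 27 becomes 26). Some participants will have a Week 0 value below 130 mg/dl, and the text should say that they remain eligible on their screening value.

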### Exclusion criteria

Having a history of unstable angina, myocardial infarction, transient ischemic attack, cerebrovascular disease, coronary artery bypass surgery, coronary intervention, or abdominal aneurysm within 3 months prior to screeningUse of statins, ezetimibe, fibric acid derivatives, proprotein convertase subtilisin/kexin type 9 (PCSK9) inhibitors, cholestyramine, nicotinic acid, omega-3 fatty acids, systemic steroids, diuretics, amiodarone, and cyclosporin, which can affect the lipid profile within 4 weeks prior to screening (however, the use of 4 g omega-3 fatty acids or less per day and short-term use of 6 mg or less per day of dexamethasone or equivalent corticosteroids within 5 days, which would not affect lipid levels, are allowed [19, 20])Uncontrolled hypertension with systolic blood pressure of more than 180 mmHg or diastolic blood pressure of more than 110 mmHgUncontrolled diabetes mellitus with HbA1c of more than 9% or fasting blood glucose of more than 160 mg/dlUncontrolled thyroid function (thyroid-stimulating hormone (TSH) levels ≥ 1.5 times the upper limit of normal)TG levels of more than 500 mg/dlSevere liver or renal disease (aspartate aminotransferase (AST) or alanine aminotransferase (ALT) levels ≥ 3 times the upper limit of normal or creatinine levels ≥ 2 times the upper limit of normal)Participants with a history of alcohol abuse or drug abuse within the past yearWomen who are pregnant or lactating, or women who do not agree to use effective methods of contraception during the clinical trialParticipants with genetic problems, such as galactose intolerance, Lapp lactase deficiency, or glucose-galactose malabsorptionParticipants with known hypersensitivity to the investigational productsParticipants who had taken other investigational products within 3 monthsParticipants who are judged by investigators to be unsuitable for participation in the clinical trial for other reasons

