Drugs that can cause dramatic changes in the gut microbiome (such as antibiotics and lactic acid bacteria) should be used cautiously only if needed, to minimize the effect on the gut microorganism, which is an exploratory outcome measure of this study. For participants who are already taking lactic acid bacteria, the investigators will instruct them not to change the dose or type as much as possible during the trial. If there is any change, the investigators will record the details in the CRF.

The use of statins, ezetimibe, fibric acid derivatives, PCSK9 inhibitors, cholestyramine, nicotinic acid, omega-3 fatty acids, systemic steroids, diuretics, amiodarone, and cyclosporine, which can affect the lipid profile, and the use of drugs that can affect thyroid function such as thyroxine will be forbidden during the study period. However, the use of 4 g omega-3 fatty acids or less per day and short-term use of 6 mg or less per day of dexamethasone or equivalent corticosteroids within 5 days, which would not affect lipid levels [19, 20], are allowed.

Dietary content and the physical activity level of participants are factors that may affect the results of this trial. In addition, gut microflora is affected by recent dietary intake. Therefore, we will compare food intake and the degree of physical activity before and after 8-weeks of investigational product administration by using a 3-day food record and the validated Korean version of international physical activity questionnaire short form [22], respectively. Participants in both groups will be educated and instructed to follow dietary and exercise guidelines for hyperlipidemia using a brochure based on the Korean Guidelines for the Management of Dyslipidemia [4].

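### The cardiovascular exclusion looks back only 3 months, so a patient with an older coronary event or TIA can be enrolled and then cannot start a statin, ezetimibe or PCSK9 inhibitor for 12 weeks while remaining in the trial

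*Protocol article*

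**What the plan says.** Exclusion criteria: the first item lists seven cardiovascular conditions and procedures and ends with the limit "coronary artery bypass surgery, coronary intervention, or abdominal aneurysm within 3 months prior to" screening. The last item lets investigators exclude anyone "judged by investigators to be unsuitable for participation in the clinical trial for other reasons".

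Inclusion criteria: age 19 to under 65 and LDL-C from 130 to 250 mg/dl. There is no separate LDL-C ceiling for patients with past cardiovascular disease.

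Interventions: statins, ezetimibe, fibrates, PCSK9 inhibitors, cholestyramine and nicotinic acid, among other drugs, "will be forbidden during the study period". The ban does not distinguish the arms. Omega-3 fatty acids up to 4 g per day are allowed.

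Study design: "The study period will include 8 weeks of medication and 4 weeks of follow-up".

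Background: on drug treatment in general, "The use of conventional medication is based on a comprehensive assessment of cardiovascular disease risk and LDL-C levels". On waiting for lifestyle change first, "conventional medication should be considered when LDL-C levels are still high after several weeks or months of lifestyle changes in patients without cardiovascular diseases". On the evidence for the study drug, "no studies have been conducted to evaluate its effect on blood lipid metabolism compared to placebo in patients with hyperlipidemia".

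**The concern.** The Background names two determinants of drug treatment: cardiovascular risk and LDL-C. The eligibility criteria limit LDL-C with a cap of 250 mg/dl, which the Discussion justifies partly by participants being off conventional lipid-lowering drugs. For a past coronary event or TIA, the only specific limit is the 3-month window.

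A past infarction, unstable angina, TIA, bypass operation or coronary intervention marks the kind of patient for whom the Background's risk-based reasoning least supports a period without the main lipid-lowering drugs. Both arms receive lifestyle education plus granules. One set of granules is placebo, and the other has not, by the article's own account, been compared with placebo for blood lipids in this condition. Neither arm offers an established substitute. What is at stake is the safety of those participants, not the validity of the analysis.

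**Working it through.** **Step 1: can such a patient pass the criteria?** Take, for illustration, a 60-year-old with an infarction 4 months before screening, LDL-C of 160 mg/dl and no listed lipid drug in the previous 4 weeks.

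| Criterion | Result |
|---|---|
| Age 19 to under 65 | met |
| LDL-C 130 to 250 mg/dl | met |
| Listed cardiovascular event within 3 months | not triggered (4 > 3) |
| Listed lipid-affecting drugs within 4 weeks | not triggered, if diuretics, amiodarone and the other listed drugs are also absent |
| Blood pressure, HbA1c, glucose, TSH, TG, liver and renal limits | may be satisfied |
| Remaining specific exclusions (alcohol or drug abuse, pregnancy, lactose-related disorders, hypersensitivity, other trials) | may be satisfied |
| Investigator judgment | discretionary; names no such case |

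The patient can meet every specific criterion. No other specific item excludes an older event.

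The point rests on the dated items: unstable angina, infarction, TIA, bypass surgery and coronary intervention. Cerebrovascular disease and abdominal aneurysm can be read as continuing states that still exclude, so they are left aside. It is grammatically possible, but unnatural, to attach the 3-month limit to the aneurysm alone.

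**Step 2: how long does the drug ban last?** The inputs are the 8 weeks of medication and 4 weeks of follow-up in Study design.

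- Study period: 8 + 4 = 12 weeks in both arms. This agrees with the last assessment at week 12 in Efficacy outcomes. The screening interval would come on top; the text does not give its length.
- Share of that period without study granules: 4/12 = 33%. In those weeks both arms have neither the granules nor the main lipid drugs.
- Event just beyond the limit: 3 months is about 13 weeks, and 13 + 12 = 25. The ban then runs from about week 13 to about week 25 after the event, later by the screening interval.

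The 4 drug-free weeks before screening are an eligibility condition. They are not added to the 12.

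**Step 3: compare with the Background.** The lifestyle-first wait is described for patients without cardiovascular disease. The patient in step 1 has had a coronary event and would spend 12 weeks on lifestyle advice and granules. The article gives no reason for extending the wait to that patient.

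**Step 4: what would exclusion cost?** Trial status plans recruitment from January 15 to December 31, 2020, which is 351 days for 30 participants: 351/30 = 11.7, or about 12 days per participant. This equals the delay per lost candidate only if accrual is uniform and there is no surplus of candidates. The sample size (12/(1 − 0.20) = 15 per group, 30 in total, as stated) does not depend on the criterion.

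**The case against.** The strongest objection is that the article states no standard that a 3-month window breaches. The Background does not say when drug treatment becomes mandatory after an event, nor that 12 weeks without it is unacceptable. That stands. A reader might infer that the protocol contradicts itself, but the documents do not support this: there is no explicit rule for patients with cardiovascular disease to contradict. The finding is a safety gap.

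A reader might also infer that the trial takes high-risk patients off treatment, or that the burden falls on placebo patients. Neither is supported. The article prescribes no washout, candidates must already be off the listed drugs, and the ban applies equally to both arms. Participation defers a possible new start.

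The safeguards are real. Medical and treatment history are collected at screening, risks are explained before consent, the ministry and the IRB approved the protocol, and "Participants will be allowed to withdraw from the study at any time without disadvantage". Participants who take a prohibited drug that can affect the outcome are removed on the investigator's judgment. The investigator's catch-all could keep such a patient out, and passing one criterion does not override it. But the catch-all is discretionary and speaks of other reasons, while cardiovascular history already has its own criterion with a stated limit. An investigator may reasonably read that limit as accepting an event at 4 months. Withdrawal and removal act only after enrolment, and each costs a 30-person pilot a participant.

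Finally, deleting the window is broad for remote events, such as a single TIA decades ago. It is also incomplete for current risk: stable angina, and diabetes with HbA1c up to 9%, stay eligible under the specific criteria. Both remarks are correct, and they limit what the change achieves.

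**Conclusion.** The point holds as a cheap improvement for patient safety. The written criterion admits some patients with an older coronary event or TIA, and for as long as they remain in the trial they cannot start the main lipid-lowering drugs for 12 weeks. The existing safeguards reduce this risk but do not remove it.

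The conclusion assumes the natural reading, in which the 3-month limit applies to the whole list, and that the patient satisfies the remaining criteria. The affected group is narrow. The article gives neither its share nor an event risk, so no count of patients or of harm is claimed; in a trial of 30 the number is probably small. Confidence is medium, because the step from the Background's reasoning to the choice of window is a clinical judgment.

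**What to change.** Delete the time limit that closes the first exclusion criterion, so that any history of the listed conditions or procedures excludes. This also settles the ambiguity over cerebrovascular disease and abdominal aneurysm. Make the change by an amendment that the IRB approves before implementation, as Ethics and dissemination requires, and apply it to participants not yet enrolled. A longer window would be a milder alternative, but the article gives no basis for choosing its length.

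The cost is one phrase and one amendment. A few otherwise eligible candidates are lost, including some whose event was long ago, and recruitment may be slightly slower. Sample size, randomization and analysis stay as they are.
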